**S2. List of approved protocol modifications**

| **Version Number and Date** | **Ethics Committee Approval Date** | **List of Modifications** |
| --- | --- | --- |
| *1.0* | *-* | *Original submission* |
| 1.1 | 11/12/2020 | - Process to follow in case of enrolment of oncology patients - Time frame for obtaining consent to continue must not exceed 24 hours (previously 72 hours). |
| 1.2 | 04/03/2021 | - Study exclusion criteria updated to remove “Patients with known or suspected scurvy” - Research Coordinator changed - New RESPOND generic email address - Randomisation updated to reflect new computer-based randomisation process - Small grammatical errors corrected throughout |
| 1.3 | 06/05/2021 | - ANZCTR number added - Additional secondary outcomes added: (1) Neurodevelopmental vulnerability at 6 months post sepsis, (2) new onset AKI - Randomisation process updated, with new screenshot included to outline the electronic based method |
| 1.4 | 01/06/2021 | - Chronic renal failure removed from exclusion criteria - Addition of clinical staff to the randomisation process - Site investigator list updated - Study management committee updated |
| 1.5 | 17/09/2021 | - Primary outcome changed to time alive free of vasopressors censored at 7 days - Thiamine removed from the intervention - PedsQL added to baseline observations. - Consumer representative added - Study sites in Brazil added |
| 1.6 | 01/09/2022 | - Additional investigator added - Amended Figure 3 on page 25 – study procedures - Investigators title change - Additional safety features and interim analysis plan - Added exclusion medications - cyanocobalamin or Deferoxamine for their co-morbid conditions - Included Sponsor/Updated Funding and duration of trial - Updated current literature - Amended follow up process - Amended DSMB Roles and Responsibilities |
| 1.7 | 08/11/2024 | - Update to Trial Steering Committee composition - Inclusion of Indian sites and investigators - Amended timeframes hospital-acquired microbiologically confirmed infection - Updated long-term follow-up processes |

ANZCTR Australian New Zealand Clincial Trials Registry; AKI acute kidney injury; PedsQL Pediatric Quality of Life Inventory; DSMB Data Safety Monitoring Board

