| Neurodevelopmental vulnerability at 6-months post-randomisation | A binary indicator of impairment if, in any of the following assessments relevant for age of the child, impairment is indicated (identified as developmental assessment >1 SD below the normative mean, or exceeding specified impairment cutoffs, as per assessment guidance):   - Pediatric Quality of Life Inventory (PedsQL) Total Score; - Ages and Stages Questionnaire, 3rd Edition (ASQ-3) Domain Scores OR Strengths and Difficulties Questionnaire (SDQ) Total Difficulties Score; - Pediatric Emotional Distress Scale (PEDS) Total Score OR Children’s Revised Impact of Events Scale (CRIES-13) Total Score; - Behavior Rating Inventory for Executive Function (BRIEF-2) Global Executive Composite Score OT Behavior Rating Inventory for Executive Function for Pre-schoolers (BRIEF-P) Global Executive Composite Score.   Assessments are completed in the order presented in the preceding sentence, aligned with order of importance. The primary analysis will use only complete assessment data (i.e. completion of all age relevant assessments). A sensitivity analysis will include patients with at least PedsQL completed, assuming that if a participant does not have complete data for any individual assessment, there will be no vulnerability assumed in that domain. Individual components of this outcome will also be presented; this is particularly relevant for PedsQL which was the only tool completed by participants recruited from Brazilian sites. |

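### The neurodevelopmental composite discards children already known to be positive, and its only stated sensitivity analysis understates prevalence by construction, so it cannot test the primary analysis

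*SAP*

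**What the plan says.** The rules are in Table S1 of the SAP supplement, under neurodevelopmental vulnerability at 6 months.

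- **Definition:** "A binary indicator of impairment if, in any of the following assessments relevant for age of the child, impairment is indicated". One positive tool is enough.
- **Order:** "Assessments are completed in the order presented in the preceding sentence, aligned with order of importance". PedsQL comes first, followed by ASQ-3 or SDQ, PEDS or CRIES-13, and BRIEF-2 or BRIEF-P.
- **Primary analysis of this outcome:** "The primary analysis will use only complete assessment data (i.e. completion of all age relevant assessments").
- **Sensitivity analysis:** "A sensitivity analysis will include patients with at least PedsQL completed". For any tool without complete data, "there will be no vulnerability assumed in that domain".
- **Brazil:** the table refers to "PedsQL which was the only tool completed by participants recruited from Brazilian sites". Section S2 records "Study sites in Brazil added" at protocol version 1.5.
- **Components:** "Individual components of this outcome will also be presented", which the table says matters particularly for PedsQL.

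The outcome is secondary: S2 lists it among the secondary outcomes added at version 1.3. The supplement gives no sample size, expected rate or missingness figure for it. The checklist in S3 places general missing-data methods and sensitivity analyses on page 13 of the main SAP text, which is not at hand.

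**The concern.** An any-positive definition and an all-complete inclusion rule do not fit together. Once one tool is positive, the composite equals 1 whatever the remaining tools would show. Requiring every tool therefore discards children whose result is known, alongside children whose result is open.

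Because the tools follow a fixed order, partial completion will mostly mean that later tools are missing. If families stop more often when the child is impaired, the complete cases are a selected, healthier group.

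A sensitivity analysis ought to reveal this. The stated one cannot, because it fills every gap with the same favourable answer. It also changes what the outcome means by site: for a Brazilian child the composite becomes PedsQL alone. At stake are the reported prevalence, the absolute difference between arms, and whether agreement between the two analyses can be read as robustness.

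**Working it through.** The plan gives no figure to reproduce, so the check is logic plus an illustration.

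**Logic**

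1. Let C mean that all age-relevant tools are completed. The primary analysis estimates P(positive | C). This equals P(positive) if C is unrelated to impairment, because known positives and undetermined children are then dropped in proportion. It differs if C depends on impairment.
2. The sensitivity analysis estimates P(at least one *completed* tool is positive). This can never exceed P(positive), and is lower whenever a missing tool would have been the only positive one. That holds even under random missingness.
3. With c the fraction complete, q the complete-case prevalence and k the share of excluded children who are known positives, the sensitivity prevalence is c × q + (1 − c) × k.

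**Illustration (all inputs assumed)**

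Four tools, 30% impaired on each, latent normal correlation 0.5, no Brazilian share, 1,000,000 simulated children per scenario. True composite: 59.0%. Stepwise completion of the four tools is 100/95/90/80% (light) or 100/90/80/65% (heavy). In the informative scenarios the chance of stopping before each later tool is doubled after an impaired PedsQL.

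| Drop-out | Complete (c) | Complete-case (q) | Known positives among excluded (k) | Sensitivity rule |
| --- | --- | --- | --- | --- |
| Random, light | 80% | 59.0% | 45% | 56.2% |
| Random, heavy | 65% | 59.0% | 44% | 53.7% |
| Doubled, light | 75% | 56.2% | 57% | 56.2% |
| Doubled, heavy | 57% | 53.2% | 54% | 53.7% |

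Check of row 1: 0.80 × 59.0 + 0.20 × 45 = 47.2 + 9.0 = 56.2%. Check of row 2: 0.65 × 59.0 + 0.35 × 44 = 38.4 + 15.4 = 53.8%, which agrees within rounding.

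Under random drop-out the primary analysis is right and the sensitivity analysis is 3 to 5 points low. Under informative drop-out both are low by similar amounts and agree with each other. With 20% impaired per tool (true composite about 44%), k under random drop-out is 31-32%.

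**Brazil**

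If a share b of children has PedsQL only, the sensitivity prevalence is (1 − b) × (rate elsewhere) + b × 30%. The document does not give b. Taking 56.2% elsewhere, b = 10% gives 0.90 × 56.2 + 3.0 = 53.6%, and b = 30% gives 0.70 × 56.2 + 9.0 = 48.3%.

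**Between-arm contrast**

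A second set of assumed inputs used 15% against 11% impaired per tool, with 5% stopping at random before each later tool. The true risk difference was 0.078. Complete cases gave 0.078. The sensitivity rule gave 0.071, 0.068 and 0.065 at Brazilian shares of 10, 20 and 30%. The risk ratio barely moved (about 0.78 true, 0.77-0.78 under the rule).

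**Retaining known positives without imputation**

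Adding them to the complete cases gives [c × q + (1 − c) × k] / [c + (1 − c) × k]. Light: 56.2 / (80 + 9.0) = 63%. Heavy: 53.7 / (65 + 15.4) = 67%. Both exceed the true 59%, so this step alone is no remedy.

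**The case against.** Four points can be made for the plan, and much of each stands.

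- **A reader might infer that both analyses are biased.** The document does not support that. Complete-case prevalence is exact when completion is unrelated to impairment, and no missingness figure is given to show otherwise. The 44-45% of excluded children who are known positives measures lost information, not bias. S5 also provides telephone interviews where parents cannot complete the online questionnaires, which should limit drop-out.
- **A reader might infer that excluding Brazil breaks the randomised comparison.** It does not in itself. Brazilian children lack the other tools, so no sound composite can be formed for them. The cost is precision and generalisability, and Table S1 already plans to present PedsQL separately for this reason.
- **A reader might infer that unequal completion between arms would produce a false effect of about 3 points.** With 85% against 75% completion, that size arises only if every non-completer loses all three later tools at once: 0.85 × 59 + 0.15 × 30 = 54.7% against 0.75 × 59 + 0.25 × 30 = 51.8%. With assumed stepwise losses (95/90/85% against 92/84/75%) it is roughly half that, 56.5% against 55.0%. The gap between arms is itself an assumption.
- **The main SAP may hold more.** Its missing-data section is not shown and may specify multiple imputation. This limits how far one can say that nothing else is planned. It does not change the two rules that Table S1 fixes for this particular outcome.

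None of this rescues the sensitivity analysis: its downward error follows from the rule itself.

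**Conclusion.** The point holds as one that should be fixed, for a single secondary outcome. The trial's primary outcome is unaffected.

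Two statements are firm and need no assumed numbers. First, the complete-data rule excludes children whose composite is already determined as positive, and all Brazilian participants unless PedsQL were a child's only age-relevant tool, which the document does not suggest. Second, the sensitivity rule can only lower prevalence, makes the Brazilian composite equal to PedsQL alone, and is not a valid robustness check.

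One statement is conditional: the primary analysis is open to selection bias if completion depends on impairment. In the illustration that costs 3 to 6 points (53-56% against 59%), with the sensitivity rule at 54-56% whether or not the primary analysis is biased. These sizes rest on four tools, 30% impaired on each, correlation 0.5 and the drop-out patterns shown; the direction of the sensitivity error does not.

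**What to change.** 1. At sites that administered the full set, score a child as vulnerable if any completed tool is positive. In the same analysis, multiply impute the missing tool scores of children whose completed tools are all negative, using completed tools, baseline PedsQL, age band, site and arm. Do not take the first step without the second.
2. Use this in place of the sensitivity analysis that assumes no vulnerability, or make it the primary analysis of this outcome with complete cases as the sensitivity analysis.
3. If the existing rule is kept, label it a best-case bound and pair it with a worst-case bound that counts undetermined children as vulnerable. In the random drop-out illustration the pair spans 56% to 0.80 × 59 + 20 = 67% (light), or 54% to 0.65 × 59 + 35 = 73% (heavy).
4. Do not form the composite for Brazilian participants from PedsQL alone. Keep the PedsQL impairment indicator, already planned as a component, as the between-arm comparison across all sites.
5. Align the wording with the general missing-data section of the main SAP.

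The cost is SAP wording and one imputation model, with no new data. The downside is that the results rest on a missing-at-random assumption. The change should be made before outcome data are analysed.
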